**Methods:**

Single-centre randomised controlled parallel group trial. Randomisation by website using computer generated concealed tables. Setting: University hospital in UK. Participants: 128 patients with acute primary hip fracture listed for operative repair under spinal anaesthesia and aged > 65 years. Intervention: Stroke volume guided intra-operative fluid management. Continuous measurement of SV recorded by a calibrated cardiac output monitor (LiDCOplus). Maintenance fluid and 250 ml colloid boluses given to achieve sustained 10% increases in stroke volume. Control group: fluid administration at the responsible (blinded) anaesthetist's discretion. The intervention terminates at the end of the surgical procedure and post-operative fluid management is at the responsible anaesthetist's discretion. Primary outcome: length of acute hospital stay is determined by a blinded team of clinicians. Secondary outcomes include number of complications and total cost of care.

Funding NIHR/RfPB: PB-PG-0407-13073.

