## Methods

### Study Objectives

#### Primary Aims

To investigate whether stroke volume (SV) guided fluid therapy for patients undergoing fractured hip surgery under a spinal anaesthetic affects:

1) the time the patient spends in acute care in hospital;

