#### Secondary Aims

2) To investigate if using SV guided fluid therapy a patient receives while having their fractured hip repaired under a spinal anaesthetic affects:

a. the time until the patient is medically well enough to be discharged from hospital;

b. the number of postoperative complications;

c. the total amount of intravenous fluid given during surgery;

d. the total cost of care.

3) To characterise the changes in the way the heart and blood vessels work after a spinal anaesthetic, as measured by minimally-invasive cardiac output monitoring.

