### Statistics

Data will be analysed by the research team in conjunction with a medical statistician, using latest versions of StatXact software. There will be no interim analysis.

From previous examination of the Nottingham Hip Fracture Database (which has over 7000 patients) it is expected that the primary outcome, length of stay (LOS), will be normally distributed following a log transformation. Following transformation these data will be analysed using ANOVA using the stratification risk categories. The primary outcome measure is time until declared medically fit for discharge. Length of acute hospital stay, superspell (total time in hospital including rehabilitation) will be analysed similarly.

The secondary outcomes of complications, residence and place of discharge will be treated as categorical and differences between the groups will be examined using loglinear analysis. Mortality outcome will be analysed using Kaplan-Meier mortality curves and log rank tests..

All secondary variables will the presented using descriptive statistics. In addition to the calculated values, confidence intervals and odds-ratios will be presented when appropriate. All clinical information including all adverse events will be presented in full. All secondary analyses will be interpreted with caution as the sample size calculation is based on the primary outcomes only. However, the level of power associated with secondary results will be investigated.

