Most studies into peri-operative interventions for fractured hip repair report outcomes focusing on length of hospital stay or 30-day postoperative mortality. In addition to length of hospital stay, our study includes time to being medically fit for discharge as a primary outcome measure. Both these outcome measures are collected by members of the research team blinded to treatment allocation. Although both primary outcomes are relevant, they are affected by many other clinical and non-clinical factors, including availability of physiotherapy services, pre-fracture morbidity and mobility, and family/social services support. The secondary end-point in our study of post-operative complications is aimed more specifically at determining the effects of the anaesthetic intervention under investigation in the study.

Although the original studies of stroke volume guided fluid therapy showed clinically important results there has been variable uptake of the technology in UK clinical practice. This may reflect changes in clinical practice, such as earlier surgery and prescription of routine intravenous fluids before surgery, which might be expected to reduce the fluid deficit by the time the patients arrive in theatre. In addition the technology used in the original studies is not suitable for use in patients who are awake. We therefore felt that it was timely to investigate this approach in contemporary clinical practice. The choice of cardiac output monitoring (LiDCOplus) in our study was pragmatic based upon validity and availability. At this time there are a limited number of calibrated minimally invasive devices suitable for this purpose. Non- or minimally invasive devices that do not require calibration are available and may be used for goal-directed intra-operative fluid management, provided the alternative system has the ability to accurately predict fluid responsiveness.

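### The primary outcome is not uniquely identified: the article names acute length of stay, time until medically fit, and both

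*Protocol article*

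**What the plan says.** All of the statements below are in the current text of the Protocol article.

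- **Abstract, Methods:** "Primary outcome: length of acute hospital stay is determined by a blinded team of clinicians".
- **Primary Aims:** one item only, "the time the patient spends in acute care in hospital".
- **Secondary Aims, item 2a:** "the time until the patient is medically well enough to be discharged from hospital".
- **Statistics, first mention:** "it is expected that the primary outcome, length of stay (LOS), will be normally distributed following a log transformation".
- **Statistics, same paragraph:** "The primary outcome measure is time until declared medically fit for discharge", followed directly by "Length of acute hospital stay, superspell (total time in hospital including rehabilitation) will be analysed similarly".
- **Discussion:** "In addition to length of hospital stay, our study includes time to being medically fit for discharge as a primary outcome measure". The same paragraph then speaks of two primary outcomes.

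The Statistics section also uses the plural when it says which outcomes the sample size rests on. The section on sample size and justification gives a mean of 17 days and an SD of 4.9 days for length of acute stay. It seeks a 3-day reduction with 90% power at α = 0.05, which it says needs 58 patients per group, and it randomises 64 per group. It gives no mean or SD for time until medically fit.

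**The concern.** A confirmatory trial needs one identifiable main test, or a stated rule for combining several. Here the same variable is secondary in the aims, the sole primary in one sentence of Statistics, and one of two primaries in the Discussion. A reader of the final report could not tell from this article whether the outcome presented as primary was the one planned.

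Two things are at stake:

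- **Error rate.** With no single primary fixed, the choice could follow the results, or success could be claimed on whichever outcome reaches significance.
- **Power.** The sample size was derived from acute length of stay. If the later sentence in Statistics governs, the 90% power was calculated for a different variable.

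**Working it through.** **1. Are the two outcomes the same variable under two names?** The aims place one as primary and the other as secondary. Statistics names one as primary and says the other is analysed in the same way. The Discussion presents one as additional to the other. So the article treats them as distinct, and its statements about which is primary cannot all be true:

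| Place | Acute length of stay | Time until medically fit |
|---|---|---|
| Abstract | primary | not named |
| Primary and Secondary Aims | primary | secondary |
| Statistics, first mention | primary (as length of stay) | not named |
| Statistics, later sentences | analysed similarly | primary |
| Discussion | primary (as length of hospital stay) | primary |

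**2. The plan's own sample size.** Inputs from the sample size section are δ = 3 days, SD = 4.9 days, α = 0.05 and power 0.90. Two-sided testing is assumed because sidedness is not stated.

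- Normal approximation: n = 2 × [SD × (z₀.₉₇₅ + z₀.₉₀) / δ]² = 2 × [4.9 × (1.960 + 1.282) / 3]² = 56.06, so 57 per group.
- t-test version: 57.04, so 58 per group, as stated. Power at 58 is 0.905.
- A one-sided test would need only 46, which does not fit the stated figure.
- Dropout: 58 × 1.1 = 63.8, so 64 per group, as stated.

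The figure therefore reproduces as one two-sided test at 0.05 on acute length of stay.

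**3. Error rate if success on either outcome counted.** Each outcome is tested two-sided at 0.05, with no true effect on either. For independent tests the family-wise error is 1 − 0.95² = 0.0975. For correlated tests it is 1 − P(|Z₁| < 1.96 and |Z₂| < 1.96) under a bivariate normal distribution. The article gives no correlation, so the values of ρ are assumptions:

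| ρ | Family-wise error |
|---|---|
| 0 | 0.0975 |
| 0.5 | 0.091 |
| 0.8 | 0.078 |
| 0.9 | 0.070 |
| 0.95 | 0.065 |
| 0.99 | 0.057 |

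A planned discharge normally follows the declaration of fitness, so the first duration is largely contained in the second. The realistic rows are those from 0.8 upwards, giving about 6% to 8%.

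**4. Rules that hold the error at 5%.** Fixing one primary, testing in a fixed order, or requiring both outcomes to succeed each keeps it at 0.05. A Bonferroni split at 0.025 each also does so. On the acute-stay inputs that split needs 68 per group by t-test before dropout, and power at 58 per group falls to about 0.85.

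**5. Power if time until medically fit is primary.** No mean or SD for it is given, so power cannot be computed in either direction.

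**The case against.** The strongest reply is that nothing in the article says success on either outcome would count. A reader might infer from the competing statements that the 5% error rate is already lost, and might take 9.8% as its size. The documents do not support that. Inflation arises only under an either-one rule or a choice made after seeing results, and 9.8% requires zero correlation between two durations measured in the same patients. This part of the reply stands.

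A second reply is that the two outcomes may be closer than they look. The Abstract says a blinded team determines length of acute stay. The only team decision described, under Randomization and Blinding, is that the patient is medically fit because no acute care need remains. On that reading the Abstract's outcome could in practice be time until medically fit. The sample size section also mentions the two side by side when describing earlier studies. This shows that the end point of acute stay needs defining, and that the Abstract is weaker support for acute stay than it first appears. It does not remove the contradiction, because Secondary Aims, Statistics and the Discussion all keep the two apart.

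Third, multiplicity rules are often left to a full protocol or analysis plan, so their absence from an article is not a fault in itself. That is fair. But an unseen plan naming one primary would still contradict part of this text.

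Finally, there is no interim analysis and the allocation sequence stays hidden until datalock. These limit when a selective choice could be made, but do not prevent one afterwards.

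**Conclusion.** The point holds as a failure to identify the primary outcome. It needs correcting before datalock, because following the text literally leads to incompatible confirmatory tests.

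The effect on error is conditional. It would be about 6% to 8% if either outcome could count at 0.05 and the correlation lies between 0.8 and 0.99 (assumed), with 9.8% the limit at zero correlation, and 5% if one primary is fixed or both must succeed.

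The power point is also conditional. A reader might infer that the trial is underpowered for time until medically fit. The documents do not show that; they only give no figures to support 90% power for that outcome. For acute length of stay the stated 58 per group is reproduced.

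**What to change.** Before allocation is revealed at datalock:

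1. Name one primary outcome.
2. Define its end point: the team's declaration of fitness, or actual discharge from acute care.
3. Use it consistently in the Abstract, Primary Aims, Secondary Aims, Statistics, the sample size section and the Discussion. Remove the plural references to primary outcomes.
4. Make the other outcome secondary, or second in a fixed testing hierarchy.

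The choice belongs to the investigators. Acute length of stay is best supported by Primary Aims and the sample size section. If it is chosen, confirm that the 17-day mean and 4.9-day SD describe the end point as defined. If time until medically fit is chosen instead, restate the sample size justification with that variable's own mean and SD.

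The cost is wording in the protocol or analysis plan. The downside is that one outcome loses primary status. Recruitment was still under way when the article was written (August 2011), so on the article's account the change could be made blind to results by group.

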### Randomization and Blinding

Randomisation (on a one-to-one allocation basis) is via a password-protected web based randomisation service provided by the Clinical Trials Support Unit and the sequence not revealed until datalock. To achieve similar numbers and balance on risk, patients will be stratified according to predicted 30-day mortality (2 levels). The Nottingham Hip Fracture Score [22-24], is used to identify patients with low (≤ 10%) or high (> 10%) risk of mortality within 30-days. Subjects are randomised on arrival in the anaesthetic room to minimise the risk of medical or surgical cancellation after randomisation.

Patients, orthopaedic surgeons and ward staff are blinded to the treatment intervention. The operative attending anaesthetist is not blinded to the treatment arm, but is blinded to the cardiac output measurements for the control arm. Postoperative data collection is by a research nurse blinded to treatment allocation. The decision that a patient is medically fit for discharge is made by the multiprofessional team when all are satisfied that the participant has no ongoing needs for acute hospital care. This team is blinded to participant allocation.

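### Mortality log-rank test names no stratum, and the complication model does not mention it, although randomisation is stratified by predicted mortality: a small, free gain

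*Protocol article*

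**What the plan says.** Under Randomization and Blinding, allocation is one-to-one and "patients will be stratified according to predicted 30-day mortality (2 levels"): low risk is a predicted risk of at most 10% on the Nottingham Hip Fracture Score, high risk is above 10%.

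The Statistics section uses this factor for length of stay: "Following transformation these data will be analysed using ANOVA using the stratification risk categories". The remaining stay outcomes, including the superspell, are to be handled in the same way.

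For death the whole specification is: "Mortality outcome will be analysed using Kaplan-Meier mortality curves and log rank tests". For complications, residence and place of discharge, the outcomes "will be treated as categorical and differences between the groups will be examined using loglinear analysis". The loglinear terms are not listed.

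Secondary aim 2 lists "b. the number of postoperative complications" as the quantity of interest. The Statistics section adds: "All secondary analyses will be interpreted with caution as the sample size calculation is based on the primary outcomes only". The sample size section says that the trial is not powered for mortality.

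**The concern.** When randomisation is balanced within risk groups, the difference between those groups no longer contributes to the chance difference between arms. A test that ignores the groups still counts that variation as noise. Its standard error is then slightly too large, so its type I error falls below the nominal level and some power is lost.

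The same section names the risk categories for stay and then describes the mortality test without them, although the categories are defined by predicted mortality. A reader following the text would run an unstratified test.

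For complications there is a second, separate looseness. The aim speaks of a number, while the analysis treats the outcome as categorical. Any complication versus none, grouped counts per patient, and a table by type of complication are all categorical, but they answer different questions. The text does not say which is meant, or that each patient enters once.

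At stake are a little efficiency and a clear secondary endpoint, not the validity of the trial.

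**Working it through.** **1. The plan's own figures.** The target of 58 per group rests on stay: a 3-day difference, SD 4.9, 90% power, α = 0.05. The exact two-sided t test gives power 0.8998 at 57 per group and 0.9048 at 58, so 58 reproduces; 58 × 1.1 = 63.8 gives 64. This does not depend on how death or complications are analysed. At 64 per group, power for 10% versus 5% mortality is 18.7%, in line with the article's statement that mortality is unpowered.

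**2. Assumptions.** The article gives neither stratum sizes nor stratum-specific rates. The ranges used were:
- high-risk share w: 20%, 30%, 40%;
- control 30-day mortality, low/high risk: 6%/18% or 5%/25%;
- control complication rate, low/high risk: 50%/70% or 45%/80%;
- mortality effect: hazard ratio ln(0.95)/ln(0.90) = 0.487, the article's 10% to 5%;
- complication effect: odds ratio 0.29, which roughly halves the overall rate (for example 54% to 26%).

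**3. Approximation by hand.** Treat the outcome as binary with low- and high-risk rates p_L and p_H, and overall rate p = (1 − w)p_L + w·p_H. The share of outcome variance between strata is

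R² = w(1 − w)(p_H − p_L)² / [p(1 − p)].

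With balance within strata, the unstratified test at 1.96 has actual size 2[1 − Φ(1.96/√(1 − R²))].

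- Mortality 6%/18%, w = 0.3: p = 0.096; R² = 0.00302/0.0868 = 3.5%; 1.96/√0.965 = 1.995; size 4.6%.
- Mortality 5%/25%, w = 0.3: p = 0.11; R² = 0.0084/0.0979 = 8.6%; 1.96/√0.914 = 2.050; size 4.0%.
- Complications 45%/80%, w = 0.4: p = 0.59; R² = 0.0294/0.2419 = 12.2%; 1.96/√0.878 ≈ 2.091; size about 3.7%.

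**4. Simulation, 128 patients balanced within strata.** Mortality: log-rank test, follow-up censored at 30 days, 4,000 trials per setting. Complications: one yes/no outcome per patient, with a Cochran–Mantel–Haenszel test standing in for a model that carries the stratum, 20,000 trials per setting. Ranges are over the six settings for each outcome.

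| | Without stratum | With stratum |
|---|---|---|
| Mortality, type I error | 3.7–4.7% | 4.6–5.2% |
| Mortality, power | 14–20% | 15–22% |
| Complications, type I error | 3.5–4.4% | 4.7–5.4% |
| Complications, power | 85–91% | 89–92% |

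Compared setting by setting, the power gain is 0.8 to 2.7 points for mortality and 0.6 to 3.9 points for complications. The simulation standard error of a 5% rate is √(0.05 × 0.95/4,000) = 0.34 points for mortality and √(0.05 × 0.95/20,000) = 0.15 points for complications. Stratified type I error is therefore at or close to 5%. Both tests were run on the same simulated trials, so the comparison between them is tighter than these errors suggest.

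**The case against.** The strongest reply is that this is a journal article. Whether a secondary log-rank test is stratified, and which terms a loglinear model holds, are details usually left to the analysis plan, which is not shown. On this view nothing is stated wrongly, and silence is not exclusion.

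For complications that reply stands. A reader might infer that they are analysed without the stratum, but the text does not support this: loglinear analysis is a multiway method that can carry treatment, outcome and risk category together. For mortality it stands only in part. The same section does name the stratum for stay, then gives the mortality method without it.

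Other stronger readings also fail:
- That only the primary ANOVA uses the risk categories. The other stay outcomes are to be analysed in the same way.
- That patients with several complications will be counted several times. This would follow only from a table by type, which the article does not describe.
- That the categorical analysis cannot address the aim. It can if the categories are grouped counts per patient; the coding is simply not given.
- That the risk score is the strongest predictor of death. The article says only that it is used to separate low from high predicted risk.

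It is also true that the effect is small and that secondary results are already to be read with caution.

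**Conclusion.** The point holds as a minor improvement to two secondary analyses. The mortality test, as stated, does not use the factor on which randomisation was stratified; the complication analysis leaves its use open, and its coding is not matched to the aim.

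A reader might infer that the unstratified tests are invalid or give too many false positives. The opposite holds: they remain valid and slightly conservative, at about 3.5–4.7% instead of about 5%. The gain from using the stratum is about 1–3 points of power for mortality, which stays near 20% either way, and about 1–4 points for complications. These sizes rest on stratum shares and event rates that the article does not give; a stronger contrast between risk groups would raise them and a weaker one would lower them. The stated sample size is unaffected, and no conclusion of the trial is threatened.

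**What to change.** In the Statistics section or the analysis plan, before the data are unlocked:

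1. State that the log-rank test is stratified by the two randomisation risk categories. Kaplan–Meier curves can still be shown by arm.
2. State that the complication analysis includes the risk category. In loglinear terms, the model contains treatment × risk and risk × complication, and the test is of treatment × complication.
3. Say whether the complication endpoint is any complication, the number per patient (with its categories if grouped), or both. Make each patient one entry and bring the wording of aim 2b into line.

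The cost is wording only. The risk category is already recorded for every randomised participant, and no patients, data or sample-size figures change. A Cox model, a count model or use of the full score would be matters of preference and are not needed to settle this point.

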### Sample size and justification

Previous studies of optimisation strategies have demonstrated approximately 30% reduction on acute length of stay or time until medically fit to discharge and approaches towards 50% reductions in complications in survivors.

Length of acute hospital stay in our unit is consistently around 17 days (SD 4.9 days), so to find a 3 day reduction in LOS in survivors would require 58 patients in each group with 90% power and α = 0.05. Assuming a 10% drop out rate (conversion to general anaesthesia, operative cancellation after randomisation etc.) we aim to randomize 64 subjects in each group. This would also provide the same power to find a 50% reduction in complication rates between the two groups. The study will not be powered to demonstrate differences in mortality (a 50% reduction in 30-day mortality from 10% to 5%, would require around 450 patients in each group).

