## Abstract

**Background:**

Approximately 70,000 patients/year undergo surgery for repair of a fractured hip in the United Kingdom. This is associated with 30-day mortality of 9% and survivors have a considerable length of acute hospital stay postoperatively (median 26 days). Use of oesophageal Doppler monitoring to guide intra-operative fluid administration in hip fracture repair has previously been associated with a reduction in hospital stay of 4-5 days. Most hip fracture surgery is now performed under spinal anaesthesia. Oesophageal Doppler monitoring may be unreliable in the presence of spinal anaesthesia and most patients would not tolerate the probes. An alternative method of guiding fluid administration (minimally-invasive arterial pulse contour analysis) has been shown to reduce length of stay in high-risk surgical patients but has never been studied in hip fracture surgery.

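### The stated 90% power is for a raw-day comparison in 58 survivors per group; it is not the power of the planned log-scale analysis, and the allowance that gives 64 does not cover deaths

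*Protocol article*

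**What the plan says.** All references are to the protocol article.

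- **Sample size and justification, inputs.** "Length of acute hospital stay in our unit is consistently around 17 days (SD 4.9 days"). From this the article concludes that "to find a 3 day reduction in LOS in survivors would require 58 patients in each group with 90% power", at an alpha of 0.05.
- **Same section, inflation.** A 10% drop-out rate is assumed. The examples given are conversion to general anaesthesia and cancellation of the operation after randomisation, and the list is left open with an 'etc.'. The result is that "we aim to randomize 64 subjects in each group".
- **Same section, mortality.** The remark on power for mortality takes 10% as the 30-day rate. The Abstract says of hip fracture surgery "This is associated with 30-day mortality of 9" per cent, and the Background section repeats that figure.
- **Statistics.** Length of stay is expected to be one that "will be normally distributed following a log transformation". It is then to be analysed by ANOVA with the two risk strata.
- **Definition of datasets analysed.** The Full Analysis set requires monitoring during surgery and known death and discharge dates. It is not limited to survivors.

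**The concern.** A power figure describes one test, in one population, at one sample size. Here the three do not match the rest of the plan.

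- **Scale.** The calculation uses a difference in days and an SD in days. The analysis compares log stays, so its effect is a ratio and its power depends on the SD of log stay, which is not given.
- **Numbers.** The 58 per group are survivors, but the step from 58 to 64 names only losses around the operation. In a population with 9-10% mortality at 30 days, deaths are a loss of about the same size as the whole allowance.
- **Population.** The sample size section speaks of survivors; the analysis set does not.

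A neutral result would be read against the 90%. That figure belongs to a test that is not planned and to a number of survivors that is not expected.

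**Working it through.** **Inputs from the article:** control mean 17 days, SD 4.9 days, difference 3 days (17 to 14), power 90%, alpha 0.05, 1:1 allocation, 10% drop-out, 64 randomised per group, 30-day mortality 9% (Abstract, Background) or 10% (Sample size and justification).

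**Assumptions:** a two-sided test (sidedness is not stated; a one-sided test would need 46 per group, so 58 points to two-sided); log-normal stays; drop-out and deaths as separate losses. Powers below are from the noncentral t distribution unless marked otherwise.

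**1. Reproducing the stated figure.** Standardised difference = 3/4.9 = 0.612.
- Normal approximation: n = 2 × (1.960 + 1.282)² × (4.9/3)² = 56.1, so 57 per group.
- Exact t-test: 57 per group gives 89.98% and 58 gives 90.5%. So 58 is right for a raw-day t-test.
- Drop-out: 58 × 1.1 = 63.8, so 64. In the other direction, 64 × 0.9 = 57.6 evaluable, which gives 90.3%. The 10% is therefore spent on drop-out alone.

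**2. Removing deaths as well, still in days.**

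| Deaths before discharge | Survivors per group | Raw-scale power |
|---|---|---|
| 10% | 64 × 0.9 × 0.90 = 51.8 | 87.0% |
| 9% | 64 × 0.9 × 0.91 = 52.4 | 87.4% |
| 7% (assumed) | 64 × 0.9 × 0.93 = 53.6 | 88.1% |
| 5% (assumed) | 64 × 0.9 × 0.95 = 54.7 | 88.8% |

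The assumed rows are there because 30-day mortality is not the same as death before discharge.

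**3. The planned log scale, with the article's own mean and SD.**
- Coefficient of variation = 4.9/17 = 0.288.
- Log SD = √ln(1 + 0.288²) = 0.283.
- Effect = ln(17/14) = 0.194, a ratio of 14/17 = 0.82.
- Power at 58 per group: 95.6% (normal approximation 95.9%). At 52 per group: 93.5% (normal approximation 93.9%).
- If the raw SD is instead held at 4.9 days in both groups, normal-approximation power is 95.5% at 58 and 93.3% at 52.

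**4. Sensitivity to the missing log SD** (ratio 0.82; every value but 0.283 is an assumption).

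| Log SD | Power at 58 per group | Power at 52 per group |
|---|---|---|
| 0.283 | 96% | 93% |
| 0.30 | 93% | 90% |
| 0.32 | 90% | 87% |
| 0.35 | 84% | 80% |
| 0.40 | 74% | 69% |

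Power is exactly 90% at a log SD of about 0.32 with 58 per group and about 0.30 with 52 per group. These calculations ignore any gain from fitting the risk strata.

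**The case against.** The best defence is that no stated figure is miscalculated. Both 58 and 64 reproduce. Sizing in days is common because a clinician can judge a 3-day reduction, and the ratio of 0.82 follows at once from 17 and 14. On the article's own mean and SD, the planned log-scale test has more than 90% power even after drop-out and deaths, so 90% is conservative. All of this stands.

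The deaths component is also conditional. The open-ended list of drop-out causes could be meant to include deaths. The mortality figures are for 30 days rather than for the hospital stay. The loss applies only if the analysis is confined to survivors, which neither the Statistics section nor the dataset definitions say. The first of these helps little, since 10% cannot hold both drop-out and a mortality that is itself 9-10%. The other two stand, and they are why the loss is given as a range and as conditional.

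Two stronger readings are tempting, and the article supports neither.
- A reader might infer that the trial is underpowered. That would need a log SD above about 0.30 to 0.32, and none is given; the value implied by 17 and 4.9 is 0.283.
- A reader might infer a large loss of power if deaths were entered into log stay at the date of death. The size of that loss depends wholly on when deaths occur, which the article does not say, and its sample size section speaks of survivors.

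**Conclusion.** The point holds as a mismatch between the stated power and the planned analysis. The 90% is the power of a two-sided raw-day t-test in 58 survivors per group.

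- **In days,** for the survivors to be expected from 64 randomised, it is about 87% if 10% drop-out and 9-10% deaths both apply in full, and 88-89% if deaths before discharge are 5-7%.
- **For the planned log-scale test,** it is about 96% at 58 per group and 93-94% at 52, provided that stay is log-normal with mean 17 and SD 4.9. It drops below 90% if the log SD exceeds about 0.32 or 0.30 respectively.

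The direction of the error is therefore unknown until the log SD is stated. The point concerns a figure that readers will rely on; it does not show that the sample size is too small.

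**What to change.** In Sample size and justification, restate the power for the analysis described under Statistics:

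1. Give the SD of log length of stay from the unit's database, which the article says holds over 7000 patients.
2. Give the effect as a ratio, 14/17 = 0.82, with the 3 days beside it for readability.
3. Give the expected evaluable number per group after both drop-out and deaths.
4. Say whether the primary analysis is limited to survivors, and make Sample size and justification agree with Definition of datasets analysed on this. If deaths are included, say how they enter and base the power on that.

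Replacing 90% with 87% would not be the remedy, because 87% is again a figure for a raw-day test that is not planned. The cost is one database query, a recalculation and about two sentences. No extra recruitment is called for. The only downside is that the stated power may change, in either direction.
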